## Abstract

**Purpose:**

Lung cancer screening (LCS) by low-dose computed tomography (LDCT) demonstrated a 20–40% reduction in lung cancer mortality. National stakeholders and international scientific societies are increasingly endorsing LCS programs, but translating their benefits into practice is rather challenging. The “Model for Optimized Implementation of Early Lung Cancer Detection: Prospective Evaluation Of Preventive Lung HEalth” (PEOPLHE) is an Italian multicentric LCS program aiming at testing LCS feasibility and implementation within the national healthcare system. PEOPLHE is intended to assess (i) strategies to optimize LCS workflow, (ii) radiological quality assurance, and (iii) the need for dedicated resources, including smoking cessation facilities.

**Methods:**

PEOPLHE aims to recruit 1.500 high-risk individuals across three tertiary general hospitals in three different Italian regions that provide comprehensive services to large populations to explore geographic, demographic, and socioeconomic diversities. Screening by LDCT will target current or former (quitting < 10 years) smokers (> 15 cigarettes/day for > 25 years, or > 10 cigarettes/day for > 30 years) aged 50–75 years. Lung nodules will be volumetric measured and classified by a modified PEOPLHE Lung-RADS 1.1 system. Current smokers will be offered smoking cessation support.

**Conclusion:**

The PEOPLHE program will provide information on strategies for screening enrollment and smoking cessation interventions; administrative, organizational, and radiological needs for performing a state-of-the-art LCS; collateral and incidental findings (both pulmonary and extrapulmonary), contributing to the LCS implementation within national healthcare systems.

## Introduction

Lung cancer (LC) is the leading cause of oncologic morbidity and mortality worldwide; accounting for 2.2 million new diagnoses and 1.8 million deaths in 2020 (18% of all cancer deaths) [1]. In Italy, the current prognosis of LC is as poor as 15.9% survival at 5 years after diagnosis [2]. The high mortality rate of LC is related to diagnosis in the advanced stage with limited curative options; hence, control of LC mortality is expected from secondary prevention by early diagnosis with LC screening (LCS), as well as primary prevention by smoking cessation.

Several trials demonstrated 20–40% reduction of LC mortality by low-dose computed tomography (LDCT) screening, which is increasingly endorsed by national stakeholders and international scientific societies [3, 4]. However, the translation of LCS benefits from trial to the general population is challenging, as shown by the US experience where LCS is being reimbursed through Medicare since 2015 [5]. The European Commission is shaping plans to tackle the recognized hurdles of LCS [6]:*Engagement of high-risk individuals*, usually nested in the most fragile socioeconomic strata [5, 7].*Maintaining high participation rates during the various time points*, which is tackled by the “satisfaction effect” after a first negative screen with consequent drop in the adherence to LCS [8].*Continuous quality assurance* for optimization of resources and reduction of risks (related to work up and radiation exposure)In 2021, the “Model for Optimized Implementation of Early Lung Cancer Detection: Prospective Evaluation Of Preventive Lung HEalth” (PEOPLHE) —an Italian multicentric LCS program—was launched to test the feasibility and implementation of LCS within the national healthcare system. PEOPLHE  addresses specific LCS issues (e.g., enrollment strategies, adherence to LCS rounds, and adherence to smoking cessation programs), testing the feasibility of LCS by sampling three geographically heterogeneous environments through the Italian territory. PEOPLHE is intended to describe:The impact of LCS by assessing strategies to optimize LCS workflow, radiological quality assurance and the need for dedicated resources, including smoking cessation facilities.Quantifying the impact of LCS on life expectancy of high-risk subjects by evaluating standard outcomes, including the proportion of early-stage LC, the number of limited resection surgeries, and surgical approaches performed for benign diseases.

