## Material and methods

### Study design

PEOPLHE is a three-year multicentric project supported by the Italian Ministry of Health (MOH) (RF-2019-12371462).

PEOPLHE aims at recruiting 1.500 high-risk individuals across 3 tertiary general hospitals (500 screenees for each center) that are community-based and provide comprehensive services to large populations of three Italian regions, including thoracic oncology multidisciplinary team. The multicentric design aims at exploring geographic, demographic, and socioeconomic diversities that might hamper the implementation of Italian LCS practice.

Selection criteria were derived from the NELSON trial [9], as follows: (i) 50–75 years of age; (ii) smoking habit of > 15 cigarettes/day for > 25 years or > 10 cigarettes/day for > 30 years; (iii) current or former smoker quitting < 10 years; (iiii) no history of cancer in the previous five years.

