### LDCT reading, reporting and management of nodules

A single radiologist with CAD as second reader will read LDCT scans. Pulmonary nodules will be measured with volumetric approach. LDCT outcome will be based on Lung Imaging Reporting and Data System (Lung-RADS) version 1.1 [15], with biennial round for subjects with negative LDCT, as they were demonstrated to be safe in Italian and Dutch trials and granting a 30% reduction in radiological workload [11, 16–18].

Based on previous LCS data, the screening algorithm will be set on the following LDCT intervals, according to the dominant lesion:24-month interval: Lung-RADS 1 or solid nodule Lung-RADS 212-month interval: sub-solid nodule included in the dimensional thresholds of Lung-RADS 26-month interval: solid nodules Lung-RADS 33-month interval: Lung-RADS 4AWork up: Lung-RADS 4B and 4X.

The proposed algorithm will mostly parallel Lung-RADS 1.1 scheme, except for point a) [15].

For CT findings requiring action, management will be based on multidisciplinary management per daily clinical practice.

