### Ethics

The Institutional Review Boards of each Unit approved the study protocol. Before each baseline LDCT, written information on benefits and harms of LCS will be provided and informed consent will be obtained from all screenees. The study was conducted carefully following the indication from Dlgs 101/20 on radiological screening. Participants will be informed about the goals of LCS, along with its potential positive and negative consequences and limitations.

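### The measures named for the aim of quantifying screening's effect on life expectancy cannot identify that effect; the aim should be reworded as descriptive

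*Protocol article*

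**What the plan says.** The Introduction of the protocol article lists two things the study is meant to describe. The first covers workflow, radiological quality assurance and resources. The second is "Quantifying the impact of LCS on life expectancy of high-risk subjects by evaluating standard outcomes, including the proportion of early-stage LC", and the sentence goes on to name "the number of limited resection surgeries, and surgical approaches performed for benign diseases".

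The rest of the article describes the following design:

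- **Duration** (Study design): "PEOPLHE is a three-year multicentric project".
- **Participants** (Study design): 1,500 high-risk people, 500 at each of three hospitals, all called screenees.
- **Recruitment** (Screenees enrollment): media, hospital flyers with a sign-up link, and meetings with healthcare providers.
- **Procedures** (Ethics; LDCT reading, reporting and management of nodules): consent is tied to the baseline scan and "informed consent will be obtained from all screenees". Scanning continues "with biennial round for subjects with negative LDCT".

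The Purpose paragraph of the abstract describes a program "aiming at testing LCS feasibility and implementation within the national healthcare system". Neither it, nor the abstract's conclusion, nor the closing statement of the Discussion mentions life expectancy.

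**The concern.** The sentence fixes both a target, the effect of screening on life expectancy, and the measures meant to deliver it. The two do not match. An effect on life expectancy compares how long people live with screening and without it. The named measures are one stage proportion and two kinds of surgical count. None records length of life, and the article describes nobody who is not offered screening and no outside population for comparison.

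What is at stake is what may be concluded. The Discussion says that Italian implementation is under debate and will draw on ongoing programs. An early-stage percentage that stands under a life-expectancy aim could be taken for evidence of benefit that the design cannot supply.

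**Working it through.** **1. The plan's own figure.** 3 centres × 500 = 1,500, which reproduces. The article ties no power, effect size or event count to it, so there is no further figure to check.

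**2. Target against measures.** The effect is Δ = E(years lived | screened) − E(years lived | not screened).

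- *First term:* needs time to death or vital status. No such outcome is named.
- *Second term:* needs an unscreened or external group, or a model that supplies one. None is described.
- *Early-stage share:* p = E / (E + A), with E early and A advanced cancers. It contains no time to death.
- *Limited resections:* a count of treatments, which gives no estimate of a survival effect.
- *Operations for benign disease:* a count of harm.

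Neither term of Δ can be estimated from the named measures. More participants would not change that.

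**3. How p can move when Δ = 0.** Assume 30 cancers, 30% early, so E = 9 and A = 21.

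| Change, with no death averted or delayed | E / (E + A) | Early share |
|---|---|---|
| None | 9/30 | 30% |
| 5 overdiagnosed early cancers added | 14/35 | 40% |
| 10 added | 19/40 | 47.5% |
| 15 added | 24/45 | 53% |
| No cancers added; 5 of the 21 found while early, same dates of death | 14/30 | 47% |

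**4. Survival from diagnosis would not repair the aim.** The Introduction gives 15.9% survival at 5 years. With exponential survival (assumed), λ = −ln(0.159)/5 = 0.368 per year. If diagnosis is brought forward by L years and the date of death is unchanged, 5-year survival from diagnosis becomes exp(−λ(5 − L)). For L = 1, 2 and 3 this is 23%, 33% and 48%.

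**5. Precision (secondary; all rates assumed).** Exposure is at most 1,500 × 3 = 4,500 person-years, and only if everyone joined on day one. At 2 to 6 lung-cancer deaths per 1,000 person-years without screening, that is 9 to 27 deaths. The Introduction cites mortality reductions of 20–40%, read here as hazard ratios of 0.8 to 0.6. By Schoenfeld's formula, 4(1.96 + 0.84)²/(ln HR)², a 1:1 randomised comparison with two-sided 5% and 80% power needs 631 or 121 deaths. With a hypothetical control arm of 1,500, power would be 6.5–11.9% at 0.8 and 16.1–38.9% at 0.6.

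If 1–4% of screenees have a cancer found (15 to 60 cancers) and about 70% are early, the exact 95% interval runs from 38–88% (10/15) to 57–81% (42/60). The share can be described, but loosely.

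**The case against.** The strongest reply is that nothing in the plan hangs on this clause. It sits in the Introduction, in a list of things to be described. The Methods set no mortality endpoint, test or sample size from it. The section Scientific output lists papers on the baseline round, enrolment strategies, collateral and incidental findings and the procedures they prompt. Removing the phrase would alter no procedure. This stands, and it limits the severity.

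The list of outcomes is also open-ended, and the full protocol, which is not shown, could hold a comparator or a life-years model. *Single-arm* and *self-selected* are inferences from the procedures and recruitment described. *Three-year* is the length of the project, not a stated rule for vital-status follow-up. These cautions are fair, but they do not rescue the sentence, which gives the task to measures that cannot perform it.

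Three stronger readings are tempting and are not supported:

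- A reader might infer that the early-stage share counts screen-detected cancers only and so leaves out interval cancers and those in non-attenders. The article does not state the denominator. That detail, and how other cancers are found, is commonly left to the full protocol.
- A reader might infer that a life-expectancy gain will be published. No planned paper says so.
- A reader might take the abstract's silence as a contradiction. An abstract may simply leave out an aim.

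**Conclusion.** The point holds as a mismatch between one stated aim and the design described. The early-stage share, limited resections and operations for benign disease cannot identify an effect of screening on life expectancy in about 1,500 screenees with no described comparator and no named survival or mortality outcome.

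This is a fault of identification, so it has no numerical size and needs none of the assumed rates. The examples show only that the early-stage share could go from 30% to between 40% and 53% with no benefit at all, and that the study would in any case see far fewer deaths than a mortality comparison needs.

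Severity is moderate. The feasibility, workflow, quality-assurance and resource aims are unaffected. The conclusion assumes that the article describes the design fully as regards comparator and outcomes.

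**What to change.** Replace the second aim in the Introduction with: *To describe stage distribution, type of resection and operations for benign disease among screenees, with exact 95% CIs; no inference on mortality or life expectancy will be drawn.*

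The cost is the rewording of one sentence and a less ambitious aim. The change needs no added questionnaire item and no registry or hospital-discharge look-up. Those would be new data collection in a study already approved by each Unit's review board, and the article's text does not show a need for them.

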## Material and methods

### Study design

PEOPLHE is a three-year multicentric project supported by the Italian Ministry of Health (MOH) (RF-2019-12371462).

PEOPLHE aims at recruiting 1.500 high-risk individuals across 3 tertiary general hospitals (500 screenees for each center) that are community-based and provide comprehensive services to large populations of three Italian regions, including thoracic oncology multidisciplinary team. The multicentric design aims at exploring geographic, demographic, and socioeconomic diversities that might hamper the implementation of Italian LCS practice.

Selection criteria were derived from the NELSON trial [9], as follows: (i) 50–75 years of age; (ii) smoking habit of > 15 cigarettes/day for > 25 years or > 10 cigarettes/day for > 30 years; (iii) current or former smoker quitting < 10 years; (iiii) no history of cancer in the previous five years.

### Study sites

Parma (Emilia Romagna; coordinating center), hereafter called Unit 1: Parma is a medium-sized city (about 200.000 inhabitants) in Northern Italy; its greater area comprises more than 450.000 citizens.Pavia (Lombardy), Unit 2: Pavia is a small/medium-sized city (about 70.000 inhabitants) in Northern Italy; its greater area comprises more than 500.000 citizens.Catania (Sicily), Unit 3: Catania is a medium-sized city (about 300.000 inhabitants), in Southern Italy; its greater area comprises than 1.100.000 citizens.

### Screenees enrollment

PEOPLHE enrollment focuses on a) systematic recruitment of eligible subjects, b) involvement of general practitioners (GP), c) efficiency of referral to LCS hub, and d) capacity needs.

Noteworthy, PEOPLHE was designed before the pandemic of severe acute respiratory distress syndrome coronavirus 2 (SARS-CoV-2), when the peripheral network of GPs was hypothesized to leverage LCS toward the population. However, this structure needed to be converted to cope with the increased workload following the pandemic. Furthermore, tailored approaches are needed to guarantee safe management of patients, screenees and healthcare personnel [10].

The informative campaign rolled out at different levels:*Media* level: local and institutional newspapers, social media pages, local television networks on health-dedicated shows. Dedicated informative events were hosted during national anti-tobacco days.*Hospital* level: flyers and roll-ups of the PEOPLHE trial reporting study objectives, inclusion criteria, and contacts (email, phone, and QR code toward the subscription website) were placed in the radiology and pneumology departments of the three Units.*Healthcare providers* level: dedicated conferences involving local GPs, pulmonologists, and any healthcare provider.

### Administrative and organizational needs

PEOPLHE will assess and quantify the need for dedicated healthcare providers across the full range from recruitment to LC treatment, focusing on radiology department needs, including data managers and administrative staff, radiographers, smoking cessation providers, radiologists, and multidisciplinary teams.

### Smoking cessation

Questionnaires on nicotine addiction will be filled at baseline, at 12 and 24 months, thus recording information on potential variation in the smoking habit over time. The source of information will be the Fagerstrom Test for nicotine dependence. This relatively fast test allows the stratification of four categories of smokers (ranging from low dependence to high dependence).

The PEOPLHE researchers will suggest participation to anti-smoking centres during baseline and recall rounds, providing information on access routes and contacts.

### Radiological quality assurance

The workload of LDCT and multidisciplinary management needs to be defined to estimate the required capacity to deliver a new healthcare service such as LCS.

**Radiological requirements**.

The radiological capacity includes performing CT scanners for low-dose imaging and radiologists experienced in thoracic imaging. The PEOPLHE employs highly performing CT scanners and is coordinated by medical staff with long-standing experience in LCS [11–14].

#### *CT scanning protocols*

CT examinations will be performed according to state-of-the-art technical requirements. Radiation exposure will be maintained as low as reasonably achievable, providing qualitative standards to detect and characterize pulmonary nodules using CT scanners equipped with advanced CT image acquisition systems and radiation dose reduction systems at all Units (e.g., automatic current modulation systems, high sensitivity detectors, iterative reconstruction algorithms); meanwhile, the scanner at Unit 1 will also be equipped with X-ray beam filtration for maximized reduction of radiation exposure (e.g., tin filter). Table 1 details the scanning protocols of each unit.

**Table 1 Tab1:** Technical information on the CT acquisition protocols of each unit

	Unit 1 (Parma)	Unit 2 (Pavia)	Unit 3 (Catania)
CT scanner	SIEMENS go.TOP	SIEMENS SOMATOM DEFINITION	GENERAL ELECTRIC Optima 660
Tube voltage	Sn100	100	120
Tube current	CARE kV Quality ref. mAs@120 kV = 6	CARE Kv 4D—3 mAs	Noise index 30 (10–40)
Pitch	0.8	1	0.984
Rotation time	0.33	0.5 s	0.5 s
*Reconstruction 1*			
Kernel	Br48	B50f medium sharp	Bone plus
Slice thickness	1 mm	1 mm	0.625 mm
Slice increment	0.7 mm	0.7 mm	0.625–1.250
IR	SAFIRE 3	–	–
Window	Lung	Lung	Lung
*Reconstruction 2*			
Kernel	Sa36	B31f medium smooth +	Detail
Slice thickness	3 mm	3 mm	2.5 mm
Slice increment	1.5 mm	1.5 mm	1.25 mm
IR	SAFIRE 3	–	–
Window	Mediastinum	Mediastinum	Mediastinum
*Reconstruction 3*			
Kernel	Sa36	B31f medium smooth +	Detail
Slice thickness	1 mm	1 mm	1.25 mm
Slice increment	0.7 mm	0.7 mm	0.6–1.25 mm
IR	SAFIRE 3	–	–
Window	Lung	Lung	Bone
CAD software	MM Oncology (SIEMENS Healthineers)	Nodule Detection (Philips Intellispace Portal)	Lung VCAR (General Electric Healthcare)
Volumetry measured on	Reconstruction 3	Reconstruction 3	Reconstruction 3

*SAFIRE* Sinogram affirmed iterative reconstruction

#### *Scheduling LCS*

Trial activities will be held during dedicated LCS time slots: days and daytimes will be tested, and screenees’ preferences recorded.Unit 1: different LCS slots will be tested to fulfil participants' preferences (e.g., Monday/Friday afternoon, or Saturday morning).Unit 2: dedicated LCS slot will include different LCS slots will be tested to fulfil participants' preferences (e.g., Monday/Friday afternoon).Unit 3: dedicated LCS slot will include Friday and Saturday afternoons.

Tailored appointments will be proposed for those screenees for whom participation during the abovementioned LCS slot will not be possible.

The hypothesis behind the organization of dedicated LCS time slots is that it could optimize LCS resources through and homogeneous workflow.

### LDCT reading, reporting and management of nodules

A single radiologist with CAD as second reader will read LDCT scans. Pulmonary nodules will be measured with volumetric approach. LDCT outcome will be based on Lung Imaging Reporting and Data System (Lung-RADS) version 1.1 [15], with biennial round for subjects with negative LDCT, as they were demonstrated to be safe in Italian and Dutch trials and granting a 30% reduction in radiological workload [11, 16–18].

Based on previous LCS data, the screening algorithm will be set on the following LDCT intervals, according to the dominant lesion:24-month interval: Lung-RADS 1 or solid nodule Lung-RADS 212-month interval: sub-solid nodule included in the dimensional thresholds of Lung-RADS 26-month interval: solid nodules Lung-RADS 33-month interval: Lung-RADS 4AWork up: Lung-RADS 4B and 4X.

The proposed algorithm will mostly parallel Lung-RADS 1.1 scheme, except for point a) [15].

For CT findings requiring action, management will be based on multidisciplinary management per daily clinical practice.

### Management of collateral and incidental findings

LDCT findings other than pulmonary nodules are classified as:

- “collateral findings”, which include smoking-related abnormalities such as calcifications of coronary arteries, pulmonary emphysema, respiratory bronchiolitis, and interstitial pulmonary abnormality/disease;

*Coronary artery calcification*

Coronary artery calcium (CAC) will be visually scored by a four-point severity scale (0: no CAC; 1: mild CAC—only isolated flecks within a segment; 2: moderate CAC—intermediate CAC between mild and heavy; 3: heavy CAC—continuous CAC within a segment) in each coronary artery (left main, left anterior descending, left circumflex, right coronary artery).

*Emphysema*

Emphysema will be assessed using a semi-quantitative visual scoring method based on a 5-category extent (absent, <5%, 5-25%, 25-50%, > 50%) and will include morphological description (e.g., centrilobular, paraseptal, advanced).

*Interstitial lung abnormality/disease*

Detection of nondependent abnormalities affecting more than 5% of any lung zone identified in subjects without known or suspected interstitial lung diseases (ILD) will be classified as interstitial lung abnormalities (ILA) [19]. Both ILA and ILD will be classified according to current guidelines, including evaluation of distribution (subpleural or non-subpleural), presence of fibrosis (fibrotic or non-fibrotic), and extent (5%-point scale). Frequency, morphology and extent will be recorded, as well as the number of screenees referred to multidisciplinary evaluation.

- “incidental findings”, which encompass non-smoking-related abnormalities [20].

Both collateral and incidental findings will be detailed in the LCS report and managed according to the Quality Assurance Standards prepared for the Targeted Lung Health Checks Programme from the National Health Service (NHS) England. Interventions prompted by detecting these findings on LDCT for LCS will be recorded. The discrepancy between the number of assigned Lung-RADS category “S” and the number of additional investigations will help in defining the cost-efficacy of LCS.

